**Datta Meghe Institute of Medical Sciences**

# (Deemed to be University)

## INSTITUTIONAL ETHICS COMMITTEE

**Submission of Research Synopsis/Proposal Ethics Review Checklist**

**INDEX**

*[****√*** *please select-Attached]*

## Synopsis along with the forms of the IEC

- Provisional Registration Form for Ph.D. (Doctor of Philosophy) in the

Faculty Medicine/Dentistry/Ayurveda/Nursing/InterdisciplinarySciences/Physiotherapy.

## Proforma of IEC (duly signed by Head of departmental research committee & Scientific Scrutiny Committee Chairman)

- Sample size justification
- Case history proforma (if applicable)
- Key articles
- Informed consent forms (English & Hindi/Marathi)

**Introduction:**

Distal radial fractures (DRF) is a frequent site of injury in upper extremity fracture and are amongst the mostly encountered fractures in emergency rooms (Hong et al., 2020). A DRF is typically described by fracture at a junction of the cortical bone where it is thinner and trabecular bone network with a reinforcement of around 2cm distally from the articulating surface of the radial (MacIntyre and Dewan, 2016). There is a considerable association of DRF on functional activities of patient affecting the socioeconomic costs and deteriorating standard of living (Meijer et al., 2019). The mechanism of injury follows a force axially placed across the bone with bone density determining the injury pattern along with the joint position following the magnitude and covering the direction of the force, however, maximum DRFs are the outcome of falls with the wrist extended and pronated. During the mechanism of injury, if a dorsal bending force across the distal radial is being placed then it is referred to as a FOOSH (fall onto an outstretched hand) (Hsu et al., 2020). Being most common upper limb fracture in all age groups with bimodal distribution, the DRF peaks in young men and in post-menopausal women with incidence ratio of 1:4 (Rundgren et al., 2020) (Hsu et al., 2020). Younger patients follow mechanism with higher energy trauma whereas elderly patients with associated osteoporosis follow lower energy falls. Following the variabilities in nature of injury, the distal radial fracture includes multiple classification systems based on pattern of intraarticular involvement as Frykman classification and based on mechanism of injury as Fernandez classification (Hsu et al., 2020). Simple classifications were made based on clinical appearance and often named after those who described them (Karantana et al., 2020). The term Colles’s fracture refers to the DRF involving both intraarticular and extraarticular surfaces with dorsal angulation, displacement and radial shortening, however, Smith fracture is extraarticular DRF with volar angulation. The Barton fracture is the dorsal or volar rim fracture with volar displacement and avulsion fracture of the radial styloid is referred to as Chauffeur’s fracture (Rundgren et al., 2020).

In younger people, DRF is mostly associated with fall associated during sports events and road traffic accidents (Burhani and Naqvi, 2020). The incidence of DRF in females is significantly greater than in males incorporating the menopause as responsible factor leading to osteoporosis associated with reduced bone density showing peak between the age group of 60 and 70 (Gutiérrez-Espinoza et al., 2017).

Considering the injury patterns and patient profiles being heterogenous in nature, the management line should prefer the severity of the injury, the desired functional independency of patients along with existing comorbidities. In older adults, the preferred line of management is conservative or non-operative to have good results with foundation stone of immobilisation. Surgical management options include closed reduction and application of a cast, percutaneous K-wires, open reduction and internal fixation with plates, or external fixation according to the patient requirements (Vaghela et al., 2020). Following DRF, many factors manipulate the recovery of the patient implying the age, gender, site and extent of injury, management line followed to manage the respective injury, compensations, patient’s education regarding the condition, radial shortening, and intra-articular involvement (Björk et al., 2020). Patients generally recover within 3-6 months to maximum range of motion, strength and function whether managed conservatively or surgically.

Patients with DRF after a duration of immobilisation are often referred for physiotherapy. In the clinical setting physiotherapists use disability assessment, such as range of motion and grip strength, to determine progress as well as outcomes. Hand activity requires a combination of adequate sensation, proprioception, intact neurological control and coordination, appropriate anatomical alignment, and muscle strength and flexibility (Gutiérrez-Espinoza et al., 2017). Physiotherapy interventions are techniques used to improve functional recovery following a distal radial fracture (Bruder et al., 2013). Physical therapy (PT) is of critical importance after the immobilization phase. PT is recommended for reducing pain, increasing range of motion (ROM) and enhancing muscle function and muscle strength. Early rehabilitation concentrate on oedema management, pain reduction as well as shoulder and finger motions (Björk et al., 2020). The therapeutic methods applied to attain these goals may be categorized as active or passive methods. Active treatment includes approaches in which patients has to participate actively in their treatment, such as counselling, a home exercise program (HEP), or supervised programme by a physiotherapist (Smith et al., 2004). Passive treatments relate to interventions where the patient plays a passive part during its procedure, such as mobilization of joint (JM), massage and the use of hot pack, TENS and ultrasound (Maciel et al., 2005).

The use of virtual reality (VR) technology platform in a healthcare environment has become increasingly common over the last two decades. This was rooted in clinical practice. The introduction of VR technology into traditional training has the ability to further increase the outcomes of the training. VR allows users to actively interact in real-time with a simulated environment and offers the opportunity to practice skills learned in the virtual environments to everyday life (Huang et al., 2019). VR-based training has the ability to promote implicit learning, improve variety, and involve the patient actively during the training. Such characteristics are crucial in the optimization of motor learning and could maximize the training impact.

The Leap Motion Controller is an infrared light detector developed as a means of hand gesture and motion recognition device. The corresponding software applies algorithms to the sensor data detected from the hands and generates a 3D representation of contour, position and movement. Current applications include gaming, education, maps and navigating the computer desktop. The technology lends itself to monitoring hand movement exercises used for wrist physiotherapy. However, no current research exists that investigates the feasibility and validity of using this technology.

**Aim:** To compare the efficacy of leap motion tracking device based rehabilitation and conventional rehabilitation in distal radial fracture patients.

**Objectives:**

1. To assess the effect of leap motion tracking device on pain in distal radial fracture patients.
2. To examine the effect of leap motion tracking device on range of motion in distal radial fracture patients.
3. To evaluate the effect of leap motion tracking device on muscle strength in distal radial fracture patients.
4. To investigate the effect of leap motion tracking device on functional parameters in distal radial fracture patients.

**Hypothesis:**

- **Null hypothesis:** There is no significant effect of Leap motion tracking device in rehabilitation of distal radial fracture.
- **Alternate hypothesis:** There is significant effect of Leap motion tracking device in rehabilitation of distal radial fracture than conventional physiotherapy, either equal or superseding.

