**Material and Methodology:**

**Study design:** This interventional comparative study will be carried out in the HumEn Research Lab of Ravi Nair Physiotherapy College, Sawangi (Meghe), Wardha, after approval from Institutional Ethics Committee of Datta Meghe Institute of Medical Sciences, Deemed to be University. Before inclusion, all the participants will be informed regarding the aim and procedure of research. Those participants who will meet the inclusion criteria must give the written informed consent. In an experimental study, those participants (N= 40) diagnosed with distal radial fracture will be enrolled for 6 weeks protocol. The participants will be randomly assigned in a 1:1 ratio, a 6-week therapy with leap motion tracking device and a 6-week traditional therapy. Figure 1 shows the flow chart of the study.

**Recruit Subjects(N=40**)

Subjects will be screened by inclusion and exclusion criteria, informed consent & medical history will be obtained from subjects

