**6 weeks intervention**

Conventional rehabilitation=60 min/day

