**6 weeks intervention**

Leap motion control rehabilitation=30 min/day

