**Intervention design:**

Group A:

- The carefully monitored physiotherapy program will include active exercises of wrist and hand at 34°C in a whirlpool.
- After that joint mobilization will be performed to the radiocarpal joint. Subjects will undergo grade I or II mobilization of Maitland approach during the first 2 weeks with a dosage of 1cps (cycle per second) for 1 minute.
- In the following 4 weeks, the sustained mobilization of Grade III Maitland approach in anteroposterior and posteroanterior directions will be done with the stabilization of distal radius in neutral position.
- The end range of motion will be attained and the treatment will be progressed with mobilization Grade IV technique.
- Strengthening technique will include exercises with theraband. This treatment will be performed for 60 mins per day for 5 days a week for 6 weeks.

Group B: Those subjects in experimental group with the Leap motion control will be asked to actively move their fingers from initial resting position and execute maximally the following five movements with their wrist and hand: fingers flexion and extension, flexion and extension of the thumb, wrist radial and ulnar deviation, forearm pronation and supination and wrist flexion and extension (Fernández-González et al., 2019) for 30 minutes regularly. Rehabilitation games include-

1. Rhythm game: This game is aimed at helping patients perform flexion exercises for wrist joint. The buttons fall from above as music plays in the background, and must be pushed at the right time by the player.
2. Flappy Bird Clone: It is designed for wrist flexion and extension both in which the player is asked to control a bird flying over a series of tubes before the track ends.
3. Skiing Game: It requires wrist movement i.e. either extension or flexion and wrist radial or ulnar deviation. A skier who comes down a slalom track is guided by the player and must cross the gates (Corona et al., 2018).

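### The four objectives and the null hypothesis ask about the effect of the Leap Motion device, but the trial compares two whole programmes that differ in time and content

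*Protocol*

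**What the plan says.** **Statements about the device.** The Objectives section has four items, all of one form. The first is "To assess the effect of leap motion tracking device on pain in distal radial fracture patients" and the third is "To evaluate the effect of leap motion tracking device on muscle strength in distal radial fracture patients"; the second and fourth do the same for range of motion and functional parameters. None names a comparator. The null hypothesis follows the same pattern: "There is no significant effect of Leap motion tracking device in rehabilitation of distal radial fracture".

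**Statements about programmes.** The Aim, directly above the objectives, compares rehabilitation based on the device with conventional rehabilitation. Study design randomises patients 1:1 to "a 6-week therapy with leap motion tracking device and a 6-week traditional therapy". The alternate hypothesis names conventional physiotherapy as comparator, but counts equality as well as superiority as a significant effect of the device.

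**The two programmes.** The study flow chart gives "Conventional rehabilitation=60 min/day" for control and "Leap motion control rehabilitation=30 min/day" for the experimental group. Intervention design describes Group A as active wrist and hand exercise in a warm whirlpool, graded Maitland mobilisation ("After that joint mobilization will be performed to the radiocarpal joint") and theraband strengthening, and adds "This treatment will be performed for 60 mins per day for 5 days a week for 6 weeks". Group B performs five active finger, thumb, forearm and wrist movements, with three Leap-controlled games, for 30 minutes. Its days per week are not given.

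**The concern.** Objectives and hypotheses govern what a trial may conclude. Here they ask what the device does, while the randomised contrast shows only how one package of care compares with another.

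Two consequences follow if the text is taken literally. First, a difference between the programmes would be written up as an effect of the device, although treatment time and several other components differ with it. Second, similar results in the two groups have no settled meaning. The null hypothesis as worded would read them as no effect of the device; the alternate hypothesis would read them as a significant effect, because it includes equality. One result would fit both hypotheses.

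The third objective shows the problem most clearly. It asks for the effect of the device on muscle strength, measured by grip strength, yet strengthening work is listed only for the arm without the device.

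**Working it through.** The protocol states no figure for this contrast, so there is none to reproduce. The check compares the arms as described and then bounds the difference in treatment time.

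**Listed content (Intervention design)**

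| Component | Group A (conventional) | Group B (Leap) |
|---|---|---|
| Active wrist and hand movement | yes | yes |
| Whirlpool setting | yes | not listed |
| Maitland mobilisation | yes | not listed |
| Theraband strengthening | yes | not listed |
| Leap-controlled games | not listed | yes |
| Daily time | 60 min | 30 min |
| Days per week | 5 | not stated |

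Active movement is common to both arms. Three components are listed for Group A only, the games are listed for Group B only, and daily time differs. To isolate the device, one arm would have to receive the other's time and content without the device. Neither does.

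**Treatment time**

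Inputs: 60 min/day, 5 days a week, 6 weeks for Group A; 30 min/day, 6 weeks for Group B (study flow chart and Intervention design).

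- Daily ratio: 30 / 60 = 0.50.
- Group A: 60 × 5 = 300 min/week; 300 × 6 = 1,800 min.
- Group B, upper bound at 7 days a week: 30 × 7 = 210 min/week; 210 × 6 = 1,260 min.
- Upper bound of the ratio: 1,260 / 1,800 = 0.70, a shortfall of at least 1,800 − 1,260 = 540 min.
- Days Group B would need to match Group A's weekly time: 300 / 30 = 10, more than a week contains.
- If Group B is also treated 5 days a week (an assumption): 30 × 5 × 6 = 900 min; 900 / 1,800 = 0.50.

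At the stated daily dose, then, Group B receives less treatment time however many days a week it is treated.

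**What each result would show**

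- *Group B worse:* the cause could be the device, the shorter time or the absence of a listed component.
- *Group B better:* the cause could be the device and its games, or any of the other differences in time and content.
- *Groups similar:* opposing influences could cancel. A non-significant test would not in any case establish equality.

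In none of the three does the result identify the contribution of the device. In all three it does bear on how the programmes compare.

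**The case against.** The strongest reply is that the comparator is already given. The Aim names it, the alternate hypothesis names it, Study design calls the trial comparative and randomises therapy against therapy, and Statistical analysis compares the groups at 6 weeks. On this reading 'the device' is shorthand for therapy based on it, and no section promises to separate components. Comparing unlike programmes is also a legitimate pragmatic choice.

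Much of this stands. The intended question can be recovered from the document, the design can answer it, and no test or estimate changes. But a correct Aim does not repair five statements that ask something else, and these are the statements the results will be reported against. If the wording is only shorthand, spelling it out costs nothing.

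A reader might infer that, because Group A has more time and resistance work, any advantage of Group B could not be due to those factors. The documents do not support this. They do not say that more time or resistance improves every outcome. For pain, longer sessions with resistance and higher-grade mobilisation could work the other way.

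A reader might also infer that similar results would certainly be reported as no effect of the device. The alternate hypothesis points the opposite way, so what the text supports is ambiguity.

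**Conclusion.** The point holds as an inconsistency between the objectives and null hypothesis on one side and the Aim and design on the other. Five statements (four objectives and the null) ask about the device alone. The trial can support a conclusion about the two programmes as delivered, but not about the device itself. Group B has half of Group A's daily time and at most 70% of its total time, and three components are listed for Group A only.

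This rests on two assumptions: that the listed content is complete, since nothing says Group B also receives the conventional components, and that Group B's 30 minutes is its whole daily treatment, as the flow chart indicates.

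A reader might go further and conclude that the randomised comparison is invalid or that the arms must be matched. The documents do not support that: the Aim asks for a programme comparison and the design provides one. The weight is moderate. What changes is the claim the trial may make. Stating Group B's days per week is a separate reporting detail; the conclusion does not depend on it.

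**What to change.** 1. **Objectives (all four):** 'To compare the Leap Motion based programme with the conventional programme on' pain, range of motion, muscle strength or functional parameters, respectively.
2. **Null hypothesis:** 'There is no difference between the Leap Motion based programme and the conventional programme.'
3. **Alternate hypothesis:** 'There is a difference between the two programmes.' Delete the closing clause that admits equality. Equality cannot belong to both hypotheses, and a non-significant result does not demonstrate it.
4. **Add one sentence:** 'The programmes differ in daily time and content; conclusions are limited to this comparison and will not be stated as an effect of the device.'

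The Aim needs no change. The cost is six statements reworded and one sentence added. Arms, analysis and sample size do not change. The downside is a narrower claim: the trial can no longer report an effect of the device as such.

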**Review of Literature**:

1. Héctor Gutiérrez-Espinoza et al. performed a randomized controlled trial to assess and analyse the improvement in functional status and pain in patients following the physiotherapy plan with supervision and home exercise program without supervision in distal radial fracture with an age limit of more than 60 years. The results included that as exercise program under physiotherapy supervision was more effective in short term and medium term for functional improvement for the patients with distal radial fracture.
2. Andrea Bruder et al did a systematic review on Exercise reduces impairment and improves activity in people after some upper limb fractures. In this study 13 relevant trials involving 781 participants with an upper limb fracture were identified. It concluded that the specific regimen of exercises play an evident role in decreasing impairments and improving UL function post specific UL fractures.
3. Andrea M. Bruder et al performed an observational study on physiotherapy intervention practice patterns used in rehabilitation after distal radial fracture. The study showed that after DRF, the interventional exercises are prescribed without considering the physiotherapist approach and patient’s need. The management included interventions in restoring mobility of wrist following principles of managing fracture and an approach with self-management.
4. Verica Filipova et al performed a randomized controlled trial evaluating the effectiveness of combination of physiotherapy and occupational therapy as compared to physiotherapy alone in patients with distal radial fracture treated conservatively. However, the combination of therapies showed statistically significant improvement in strength of grip as compared to only physiotherapy after the fracture. The efficacy was not supported with DASH score results.

**Material and Methodology:**

**Study design:** This interventional comparative study will be carried out in the HumEn Research Lab of Ravi Nair Physiotherapy College, Sawangi (Meghe), Wardha, after approval from Institutional Ethics Committee of Datta Meghe Institute of Medical Sciences, Deemed to be University. Before inclusion, all the participants will be informed regarding the aim and procedure of research. Those participants who will meet the inclusion criteria must give the written informed consent. In an experimental study, those participants (N= 40) diagnosed with distal radial fracture will be enrolled for 6 weeks protocol. The participants will be randomly assigned in a 1:1 ratio, a 6-week therapy with leap motion tracking device and a 6-week traditional therapy. Figure 1 shows the flow chart of the study.

**Recruit Subjects(N=40**)

Subjects will be screened by inclusion and exclusion criteria, informed consent & medical history will be obtained from subjects

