**Perform post treatment assessment**

**Statistical Analysis**

**Participants:**

Inclusion criteria are as follows:

1. Age 18-50 years, who have been referred from the Dept. of Orthopaedic.
2. Patients must be diagnosed with an A3 extraarticular multi-fragmentary distal radial fracture type and treated conservatively with plaster cast immobilization and closed reduction.
3. Participants must accept and sign the Informed consent.
4. No previous history of wrist/ hand fracture, history of inflammatory arthritis, or any possible upper limb fracture.
5. Patients who are able to comprehend (Lyngcoln et al., 2005).

Exclusion criteria are as follows:

1. Participants who were treated for DRF reduction and/or fixation with some form of surgical intervention (e.g. external fixation, volar plate, and Kirschner wires).
2. Patients with Mini-Mental score less than 26 points on the examination.
3. After the removal of the immobilization, patients with immediate complications like malunion or non-union.
4. Patients with past trauma either in arms or hands that had impaired function.
5. Patients with inflammatory or non-inflammatory diseases and neurological disorder were excluded.

**Sample size consideration:** This is an experimental study with two-group design that examines the effect of leap motion control in distal radial fracture rehabilitation. Analysis of previous power using G*Power is used to determine the same size (Engel et al., 2019). 40 participants will be enrolled to the control group or experimental group and will be allocated accordingly (Maciel et al., 2005). The G*Power analysis followed the following terms for calculation of sample size which is graphical represented in figure 2.

**t tests** - Means: Difference between two independent means (two groups)

**Analysis:** A priori: Compute required sample size

**Input:** Tail(s) = One

Effect size d = 0.8

α err prob = 0.2

Power (1-β err prob) = 0.95

Allocation ratio N2/N1 = 1

**Output:** Non-centrality parameter δ = 2.5298221

Critical t = 0.8511828

Df = 38

Sample size group 1 = 20

Sample size group 2 = 20

Total sample size = 40

Actual power = 0.9531573

**Figure 2:** The calculation of sample size using G*Power analysis

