**Statistical analysis:** The SPSS latest version will be used to perform statistical analysis. To compare the group effect, two-way repeated measures ANOVA (analysis of variance) will be used. When ANOVA reveals a significant difference, student’s t test will be used to compare the changes within the group. Statistical significance is determined by a two-sided p value of less than 0.05. Mann-Whitney U, t-test or Fisher’s exact test will be used for comparing Groups at baseline and for comparing the primary and secondary outcomes between the groups at 6 weeks.

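### Age and sex, which the protocol says affect recovery, are used neither in the stated allocation nor in the named tests; using them is a cheap improvement, chiefly for sex

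*Protocol*

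**What the plan says.** The Introduction states that "many factors manipulate the recovery of the patient implying the age, gender, site and extent of injury", among other things. The inclusion and exclusion criteria deal with much of that list: they fix one extra-articular fracture type, treated by closed reduction and plaster cast, and exclude surgery. They do not restrict sex, and they admit ages 18 to 50.

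On allocation, the Study design paragraph says "The participants will be randomly assigned in a 1:1 ratio", and the flow chart shows 20 subjects in each group. No stratification, blocking or minimisation factor is named.

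On analysis, the Statistical analysis paragraph says "To compare the group effect, two-way repeated measures ANOVA (analysis of variance) will be used". It then names a t-test, Mann-Whitney U test or Fisher's exact test "for comparing the primary and secondary outcomes between the groups at 6 weeks". None of these is given a covariate. The same paragraph plans to compare the groups at baseline but gives no use for the result. It sets the level as follows: "Statistical significance is determined by a two-sided p value of less than 0.05".

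**The concern.** Age and sex are known before allocation and cost nothing to record. The protocol itself calls them prognostic, then uses them at neither of the two stages where they could help. With 20 patients per arm, randomisation can easily leave the arms unequal on sex. If sex affects recovery, part of the observed treatment difference then reflects sex, and the named 6-week tests have no means of removing it. Variance that age and sex could explain also stays in the error term, in a trial that has little power to spare at its own significance level. Finally, a baseline comparison with no stated consequence leaves room for adjustment to be decided after the imbalance has been seen.

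**Working it through.** **Inputs from the protocol.** 40 patients, 20 per arm (flow chart); d = 0.8, one-sided, with "α err prob = 0.2" and "Power (1-β err prob) = 0.95" (Sample size consideration); two-sided 0.05 for the analysis (Statistical analysis).

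**Assumptions, because the protocol gives no figures.** Share of women 20% to 50%; effect of sex on outcome 0.3 to 0.8 SD; share of outcome variance explained by age and sex (R²) 5% to 20%.

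**1. The plan's own figure.** Two-sample t-test, noncentrality d × √(n/2) = 0.8 × √10 = 2.530, 38 df. At one-sided 0.2 the critical t is 0.851 and power is 0.953, as stated. At the two-sided 0.05 of the analysis the critical t is 2.024 and power is 0.693. That mismatch is a separate matter; 69% is the right starting point here because it belongs to the tests that will be run.

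**2. Chance of a sex imbalance.** With F women among 40 patients split 20/20, the number of women in one arm is hypergeometric(40, F, 20).

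| Women of 40 | Arms differ by ≥ 4 women (≥ 20 points) | By ≥ 6 women (≥ 30 points) |
|---|---|---|
| 8 (20%) | 23.5% | 4.4% |
| 12 (30%) | 30.1% | 8.2% |
| 20 (50%) | 34.3% | 11.3% |

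The results for 70% and 80% women mirror those for 30% and 20%.

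**3. Age.** The difference in mean age, in SD units, has standard error √(2/20) = 0.316. The chance of a gap of at least 0.5 SD is 11%.

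**4. Effect on the treatment difference.** Shift = imbalance × sex effect. For 20 points: 0.2 × 0.3 = 0.06 SD to 0.2 × 0.8 = 0.16 SD, which is 8% to 20% of d = 0.8.

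**5. Which analyses it reaches.** 8,000 simulated trials were run per scenario, with 20 women and 20 men, no treatment effect and a baseline to 6-week correlation of 0.5.
- Sex effect of 0.5 SD on recovery: the slope on imbalance is 0.50 for the 6-week difference and 0.50 for the change from baseline, so it passes in full into both.
- Sex effect of 0.5 SD on level, the same at both times: the slope is 0.53 for the 6-week difference and about 0 for the change, so it cancels in the group-by-time term of the repeated measures ANOVA.
- Type I error of the unadjusted 6-week t-test over all randomisations: 0.049 to 0.050.

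**6. Power after adjustment.** Noncentrality = 2.530 / √((1 − R²) × 37/35), with 36 df and critical t 2.028. The factor 37/35 is the cost of estimating two covariates without stratification. If sex is balanced by stratification, the factor is about 37/36.

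| R² of age and sex | Power, unstratified | Power, sex stratified |
|---|---|---|
| 0 (unadjusted) | 69.3% | – |
| 0.05 | 69.0% | 70.2% |
| 0.10 | 71.4% | 72.6% |
| 0.20 | 76.3% | 77.5% |

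**7. Do the two assumptions agree?** With equal numbers of each sex, a difference of g within-sex SD explains (g²/4)/(1 + g²/4) of the variance: about 2% for g = 0.3, 6% for 0.5 and 14% for 0.8. At the lower end of the assumed sex effect, sex alone therefore brings almost no power, and the benefit is protection against a chance imbalance.

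**The case against.** A reader might infer that an imbalance biases the trial or passes straight into every treatment estimate. The documents do not support that. Allocation is random, so the tests hold their level. The first analysis named for the group effect is "two-way repeated measures ANOVA (analysis of variance) will be used", and its group-by-time term removes any stable age or sex difference in level. Full carry-over applies to the 6-week tests, and to the ANOVA only for an effect on change. The Introduction does speak of recovery, so that route remains open, but no size is given.

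A reader might also compute power of 74% to 79% by dividing d by √(1 − R²). That leaves out the cost of estimating two covariates. Larger sex effects, such as 1.5 SD, may be imagined for grip strength, but grip is a secondary outcome, and the protocol gives no sex effect for the primary ones, DASH and range of motion. Any R² beyond what the baseline value already explains may be smaller still.

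The Introduction's sentence is general background on this fracture at all ages. The excess in women that it links to the menopause concerns incidence and peaks at 60 to 70, outside the 18 to 50 enrolled. This weakens the age part in particular.

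Unstratified randomisation is an accepted choice for 40 patients at one site, silence on stratification does not exclude it, and covariates are often left to an analysis plan that is not at hand. This stands in part. However, the protocol does fix the 6-week tests, which cannot take covariates, so a later plan would have to change that text. Stratification also has to be settled before the first allocation.

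**Conclusion.** The point holds as a cheap, optional improvement that rests mainly on sex. It is not an error that invalidates the analysis. The chance of a 20-point sex imbalance, 24% to 34%, follows from the design alone once a share of women between 20% and 50% is assumed. The shift of 0.06 to 0.16 SD depends on an assumed sex effect of 0.3 to 0.8 SD. The power gain, from 69% to about 71% to 76% (about 73% to 77% with sex stratified), depends on an assumed R² of 10% to 20%, and is about nil at 5% or below.

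**What to change.** - **Statistical analysis:** in place of the unadjusted 6-week tests, pre-specify one between-group model per outcome: 6-week value on group, baseline value, sex and age (continuous). State that it is used whatever imbalance is observed, so that the baseline comparison decides nothing.
- **Study design:** stratify the 1:1 list by sex, using permuted blocks of varying size. One factor is enough at this sample size.
- **Flow chart and Power analysis:** say about 20 per arm. In simulation, two sex strata missed an exact 20/20 split in roughly 35% of trials (block sizes 2 and 4) to 44% (sizes 4 and 6), nearly always as 19/21 and occasionally as 18/22.

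The cost is two degrees of freedom for sex and age, a second allocation list, and slightly unequal arms. No extra patients or measurements are needed.
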